### Sample size

With reference to the study conducted by Gaidhane
*et al.,
*
^
25
^
^,^
^
26
^ the expected difference in child development outcomes between the intervention and control groups is 0.5 SD, considering a dropout rate of 10%, level of significance = 5%, and power = 80%. The formula for calculating sample size for two independent means is:

$$n=\frac{2\;{\left(\mathrm{Z\alpha}+\mathrm{Z\beta}\right)}^{2}\times \delta^{2}}{d^{2}}$$
where

n = Minimum sample size required in each group,

d = Expected mean difference between two groups = 0.5

δ = standard deviation = 1.69 (As per Previous Study)

Zα: value of type I error at 5% significance level =1.96

Zβ: value of type II error at 80 % Power (1-β) = 0.84

Based on the above formula, the calculations are as follows:

$$\begin{array}{c} n=\frac{2\;{\left(1.96+0.84\right)}^{2}\times 1.69^{2}}{{\left(0.5\right)}^{2}}\\ =\frac{2\left(7.84\right)\times 2.86}{0.25}\\ =\frac{44.84}{0.25}=179.37\approx 180 \end{array}$$

Thus, the sample size required per group is 180. Hence total sample size required is 360. A sample size of 360 subjects, 180 in each arm, is sufficient to detect a difference of 0.5 between groups in developmental scores, assuming a standard deviation of 1.69 using a two-tailed t-test of difference between means with 80% power and a 5% level of significance. For assessing the changes in parenting knowledge and skills, parents of all children in intervention group
**(180)** will be assessed.

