### Objectives

*Primary objectives:*
1.To improve the motor, language, cognitive, and social-emotional development parameters of under-five years children admitted in A.V.B.R.H. through play therapy and follow-up at scheduled monthly home visits.2.To enhance the knowledge and skills of parents on early child development and improve parent-child interactions.

*Secondary objectives:*
1.To assess the effectiveness of the dedicated Play Therapy Kit specially designed for hospitalized children.2.To provide follow-up and assessment mechanisms to parents through online mode, in case the home visits are not possible.

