### Trial design

This will be a randomized controlled exploratory trial. The study participants will be randomized into Intervention and Control groups with a 1:1 ratio using block randomization.

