### Outcomes

*Primary outcomes:*
1.Improvements in mean scores of child developmental parameters for cognitive, physical, socio-emotional, and language development by the end of one year of intervention.2.Improvements in knowledge and skills of parents regarding early child development by the end of one year of intervention.

*Secondary outcomes:*
1.Improvements in the parent-child satisfaction levels regarding the in-hospitalization care and follow-up by the end of one year of intervention.

Figure 2 details the schedule of enrolment, interventions, and assessments.

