### Data collection and management

Data will be collected in pre-tested Open Data Kit (O.D.K.) based app with inbuilt checks for data quality, identifying duplicate entries. The data received on dedicated server of Research Cell of Datta Meghe Institute of Medical Sciences will be imported and checked on real time basis. The data will be encrypted for sensitive information and will be handled by the assigned team including Information Technology Coordinator and statistician. The datasets will be shared and made reusable according to FAIR data principles.

Assessments will be conducted using the tools as detailed below:
1.Physical Development (Using Developmental Milestones Checklist-II)
^
27
^
^,^
^
28
^
a.Improvement in Fine Motor scoresb.Improvement in Gross Motor scores2.Cognitive Development Scores (Using Developmental Milestones Checklist-II)3.Language Development Scores (Using Developmental Milestones Checklist-II)4.Socioemotional Development Scores (Using Profile of Socio-emotional Development)
^
29
^
5.Home Environment (Using HOME Inventory Assessment)
^
30
^
^–^
^
32
^
6.Parent-child Interactions (Using Observation of Mother-Child Interaction Tool)
^
33
^

The research assistants will be trained on the use of all these tools and inter-rater, intra-rater scoring exercises will be conducted during training. To promote participant retention and complete follow-up, all enrolled children in the intervention group will receive scheduled home visits at monthly intervals. The children in the control group will be followed up telephonically at monthly intervals. Also, telephonic follow-up will be taken for those missing home visits in intervention group. The outcome data will detail the participants who discontinue or deviate from intervention protocols.

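### Parents' knowledge and skills, a primary outcome, is to be assessed in the intervention arm, with no between-arm analysis named, so as written it is an uncontrolled before-after change

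*Protocol article*

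**What the plan says.** Under Objectives, the second primary objective is "To enhance the knowledge and skills of parents on early child development and improve parent-child interactions". Under Outcomes, the second primary outcome is "Improvements in knowledge and skills of parents regarding early child development by the end of one year of intervention".

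Under Trial design, "The study participants will be randomized into Intervention and Control groups with a 1:1 ratio using block randomization". Under Sample size, "A sample size of 360 subjects, 180 in each arm, is sufficient to detect a difference of 0.5 between groups in developmental scores". That section then turns to the parent outcome: "For assessing the changes in parenting knowledge and skills, parents of all children in intervention group", followed by the number, "180) will be assessed".

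Statistical methods plans mean differences between arms, pre-post differences and a difference-in-difference analysis. It attaches the between-arm work to child development scores (motor, language, cognitive, socio-emotional). It names no between-arm analysis for parents' knowledge and skills.

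Three other places bear on the point:

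- The section on group sessions at the hospital says that assessors contact control families for baseline and endline assessments, without saying what is assessed.
- Data collection and management lists a HOME Inventory and "Parent-child Interactions (Using Observation of Mother-Child Interaction Tool"), and names no arm for either.
- Outcomes refers the reader to Figure 2 for the assessment schedule; that figure is not available in the text reviewed.

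**The concern.** A primary outcome of a randomised trial should be measured in both arms, because the control arm shows what would have happened without the intervention. Here the sentence that fixes the assessed group names one arm and gives that arm's size.

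Over a year, parents gain experience, the child recovers and grows, and answering the same items twice can raise scores. In a one-arm before-after comparison, none of this can be separated from the effect of the programme. One of the two primary objectives would then have no randomised answer. This is not a detail that an analysis plan can settle later, because no analysis restores control data that were not collected. The child development comparison is not affected.

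**Working it through.** **Step 1. Does 180 mean one arm?** Sample size gives "d = Expected mean difference between two groups = 0.5", SD 1.69, and z values 1.96 and 0.84:

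n per arm = 2 × (1.96 + 0.84)² × 1.69² / 0.5² = 2 × 7.84 × 2.8561 / 0.25 = 179.1, rounded up to 180.

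The article's 179.37 comes from rounding 1.69² to 2.86, and it also leads to 180 per arm and 360 in total. The 180 parents are therefore exactly one arm. If both arms were meant, both the named group and the number would be wrong. This calculation is for child scores; no size is derived for the parent outcome.

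**Step 2. What can be estimated as written?** There are 180 intervention parents and no stated control parents, so only the within-arm change is available. Its expected value is the programme effect plus any change that would have occurred anyway, and the two cannot be separated.

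**Step 3. How often would a change unrelated to the programme look significant?**

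Inputs:
- From Sample size: 180 parents, 10% dropout, two-sided 5%. Pairs: m = 180 × 0.90 = 162, √162 = 12.73.
- Assumed, not in the documents: a non-programme gain g of 0.1, 0.2 or 0.3 SD, a pre-post correlation r of 0.3 to 0.7, and zero programme effect.

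Formulas: SD of change = √(2(1 − r)). Chance of a significant gain = Φ(g × √m / SD of change − 1.96).

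Example, g = 0.2 and r = 0.5: SD of change = 1.00; 0.2 × 12.73 / 1.00 = 2.546; Φ(2.546 − 1.96) = Φ(0.586) = 0.72.

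| Assumed gain | r = 0.3 | r = 0.5 | r = 0.7 |
|---|---|---|---|
| 0.1 SD | 18.8% | 24.6% | 37.6% |
| 0.2 SD | 57.6% | 72.1% | 90.8% |
| 0.3 SD | 89.7% | 96.8% | 99.9% |

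**Step 4. What would a two-arm assessment give?** Randomisation makes the expected drift unrelated to the programme equal in both arms, so it cancels in the between-arm difference. With 162 per arm and 80% power:

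- Unadjusted: (1.96 + 0.84) × √(2/162) = 2.80 × 0.1111 = 0.31 SD.
- Adjusted for baseline: multiply by √(1 − r²). At r = 0.5 this is 0.311 × 0.866 = 0.27 SD. Over r = 0.3 to 0.7 it runs from 0.311 × 0.954 = 0.30 SD to 0.311 × 0.714 = 0.22 SD.

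No extra recruitment is needed.

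**The case against.** The sentence does not say that control parents are excluded. Controls do have baseline and endline contacts, the HOME Inventory and mother-child interaction tool are listed without an arm, and Figure 2 might show parent assessments in both arms. A reader might therefore infer either that nothing about control parents is measured or that everything is. The documents support neither. Two-arm data on the skills half of the outcome are possible but not established: the hospital sessions section mentions assessment of home environment and parent-child interaction when describing the intervention arm's home visits. If Figure 2 does show both arms, it conflicts with Sample size and the two must be reconciled.

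A reader might also infer that the trial has no instrument for parental knowledge, because none is listed. A journal article may leave that to the full protocol, so it is not part of this point.

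A third tempting reading is that a false significant gain is likely. That depends on a drift that the documents do not give; at 0.1 SD it is the less likely result throughout the range shown. The article specifies no significance test for this outcome and calls the trial exploratory, so how a gain would be reported is not known.

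Finally, the remedy may come too late. Recruitment was set for January to March 2023, completion was expected on 30 May 2024, and the protocol version is dated 04/10/2024. This stands, and it affects which remedy is feasible. None of these objections supplies a between-arm comparison for an outcome that the article labels primary.

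**Conclusion.** The point holds as a defect in the written plan. Sample size confines the second primary outcome to the 180 intervention parents, and Statistical methods names no between-arm analysis for it. As written, the result is an uncontrolled before-after change that cannot support a claim that the programme improved parents' knowledge and skills.

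That conclusion rests on the text alone. The size of the risk rests on assumptions: with 162 pairs and a correlation of 0.3 to 0.7, a significant gain without any programme effect would appear in about 19% to 38% of trials for a 0.1 SD drift and about 58% to 91% for a 0.2 SD drift. Whether some two-arm data on parenting skills exist is open.

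**What to change.** First establish whether control parents were or still can be assessed. Then take the route that applies.

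1. **Control parents can be assessed.** Replace the sentence in Sample size with wording such as:

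   > Parents of all 360 children, in both arms, are assessed with the same instrument at the baseline and endline contacts. The outcome is the between-arm difference at 12 months, adjusted for baseline.

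   Add the matching analysis to Statistical methods. The cost is a short added assessment for 180 control parents at contacts already in the plan; the questions may prompt those parents slightly.

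2. **HOME and mother-child interaction scores were collected in controls.** Use them for the between-arm comparison of skills, say so under Outcomes, and reconcile Sample size with the control-group contacts, the tool list and Figure 2. They would not cover knowledge, which then falls under route 3 unless it too was measured in controls.

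3. **Control parents were not assessed and no longer can be.** Remove primary status and report a descriptive within-arm change with no effectiveness claim. On the dates in the article this may be the only route left. It costs a change of wording and the loss of one primary claim.

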### Recruitment

Parents of children reporting to A.V.B.R.H. in the first three months (January-March 2023) will be enrolled in the trial. All participants consenting to participate in the study will be assigned the Unique ID. Using a blocked randomization process with age groups as the Blocking variable, participants will be allocated to intervention or control groups. Age groups will be:
1.Six months to 30 months2.31 months to 60 months.

All children hospitalized in A.V.B.R.H., scheduled to stay for a minimum of three days in the hospital, and their parents signed the informed consent will be enrolled in the study.

### Assignment of interventions: allocation

All participants consenting to participate in the study will be assigned the Unique ID. Sequence generation will be done using computer generated random numbers. Using a block randomization process
^
10
^
^,^
^
11
^ with age groups as the blocking variable, participants will be allocated either to intervention or control groups.

Sequentially numbered, opaque, sealed envelopes will be used for implementing the allocation sequence.

The Principal Investigator will generate the allocation sequence, trained assistants will enroll the participants, and assign participants to intervention and control groups. The Principal Investigator will train the Research Assistants for intervention, and assessors for baseline-endline assessments, supervise the data collection process and monitor the trial implementation process. We will ensure that all adults associated with the trial have the appropriate permissions and training and criminal records check to work with children. The outcome assessors and data analysts will be blinded.

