### Eligibility criteria

*Inclusion criteria:*
1.Children admitted to the Paediatric Ward of A.V.B.R.H. aged six months to 60 months.2.Children from villages within 25 Km periphery of A.V.B.R.H.3.Parents consenting to the participation of their child in the Play Therapy Programme.

*Exclusion criteria:*
1.Seriously sick, moribund children with life-threatening conditions.2.Children in Intensive Care treatment.

The Investigator will take written informed consent from the parents of the hospitalized children. The comparator (control) group will include children from the adjoining paediatric ward on another floor and admitted during the period when interventions will not be implemented. Children from this group will receive all required treatment and nursing care except the Play therapy sessions. This will help to avoid any contamination. Baseline assessments and socio-demographic information of these children will be collected at enrolment. Follow-up home visits will be done at monthly home visits. Assessments will be done at six months and 12 months from the date of enrolment. If successful, the children from control group will receive play therapy after the trial is over.

The children and their parents signing the informed consent will be enrolled in the study. All enrolled children hospitalized in A.V.B.R.H., scheduled to stay for a minimum of three days in the hospital, will be assigned a Unique ID. Children will be allocated to intervention or control groups using a block randomization process
^
22
^
^,^
^
23
^ with age groups as the blocking variable. Intervention group will receive the play therapy sessions along with the required treatment and nursing care during hospitalization stay. Sociodemographic profile and baseline assessments will be done. Play therapy sessions will be conducted at the dedicated play area in hospital. Also, these children from the intervention area will receive the play sessions at scheduled monthly home visits.
Figure 1 shows the anticipated Consort Flow Diagram of study participants.

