**Figure 1. f1:**
[figure not shown]
Consort flow diagram.

The play therapy manual has been developed by the Principal Investigator with the activities specified as per the domains of child development including physical development, language and communication skills, socio-emotional development, and cognitive development. A couple of parents and children were involved and their inputs were included in the development and piloting of the Play Therapy Manual. The Play Activity manual
^
24
^ is available in the extended data.

The Principal Investigator will train the team of Research Assistants on the intervention package. The trained and certified Research Assistants will deliver the intervention in hospital setting and then at home visits as per the schedule drafted by Principal Investigator.

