### Criteria for group sessions at the hospital

The hands of parents and their children will be washed before the activities start to avoid infectious contamination. Children will be divided into two groups as below:
1.Six months to 30 months old2.31 months to 60 months.

The intervention delivery details are as below:

On first day of hospitalization, parents and children will be interacted at Paediatrics ward. Randomization will be done and the parents in intervention arm will be sensitized about Play Therapy Programme. Written informed consents of parents will be taken from those who consent for participation and will be enrolled in the programme and e-learning platform/Whatsapp group.

On second day of hospitalization, a session will be conducted at designated play area in hospital. The session will emphasize on importance of early child development, its implications; diet, nutrition and healthcare of children. This session will be followed by play interaction session on cognitive and language development.

On third day of hospitalization, a play session on motor developmental activities will be conducted. This will be followed by session on socioemotional development and activities to promote it. Relevant Documents and reading materials in local language will be shared with parents during these sessions. The enrolled children will participate in play sessions and activities till the child is hospitalized.

After discharge from the hospital, parents and children will be contacted through monthly home visits personally and if needed, through online mode (Whatapp video call/Google classroom) at monthly intervals. The home visits will be scheduled for the assessment of Home Environment and Parent-Child Interactions. The monthly sessions will be continued till one year from the date of enrolment of child in the programme. Appropriate medical and nursing care will be provided during the hospital stay. If needed, referral services will be provided during follow-up at-home visits. If Children and parents insist on discontinuing play therapy, the sessions will be discontinued for those children.

After one-year of enrollment, assessments of age-appropriate developmental milestones of children will be done either in the hospital ECD Centre or through personalized home visit to the enrolled family. Age-appropriate assessment tools will be used. Reports will be shared with parents, and follow-up instructions and meeting schedules will be shared.

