### Oversight and monitoring

*Composition of the coordinating center and trial steering committee*

The Trial Steering Committee (TSC) consist of the following:
1.The Head of the department of Public Health2.PhD Supervisor3.Director, Research and Development4.The Head of the department of Pediatrics5.Principal investigator6.Statistician7.Data manager

The Principal Investigator is responsible for all aspects of local organisation including identifying potential recruits and taking consent. The PhD Supervisor, Head of Public Health Department, Director Research and Development, and Head of Paediatrics department will be supervising the trial. Trial Steering Committee (TSC) will meet over the course of the trial to oversee conduct and progress in monthly meeting.

*Composition of the data monitoring committee, its role, and reporting structure*

The data monitoring committee (DMC) consists of Research-in-charge of the institute and Research-in-charge and Data Manager of the department. All related data will be managed and monitored by Principal Investigator, along with support from a statistical expert as per the guidance of Data Monitoring Committee. Since this is a play therapy intervention, hardly any adverse events and other unintended effects of trial interventions or trial conduct are expected. If encountered, those will be reported per the guidelines from the Institutional Ethics Committee. Project Management Group will review the trial conduct in monthly meetings. The Trial Steering Group and the independent Data Monitoring and Ethics Committee will review the conduct and progress of trial in quarterly meetings. Important protocol modifications will be communicated to relevant parties (e.g., investigators, Regional Ethics Committee/Institutional Review Boards, trial participants, and trial registries through emails and printed hard copies, as required).

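### The Principal Investigator both generates the allocation sequence and is responsible for recruitment and consent, and the article contradicts itself on whether the staff who deliver the therapy also score outcomes

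*Protocol article*

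**What the plan says.** **Allocation.** Under Assignment of interventions, the Protocol article states: "The Principal Investigator will generate the allocation sequence, trained assistants will enroll the participants, and assign participants to intervention and control groups". The concealment device is given in the same section: "Sequentially numbered, opaque, sealed envelopes will be used for implementing the allocation sequence". Under Oversight and monitoring: "The Principal Investigator is responsible for all aspects of local organisation including identifying potential recruits and taking consent". Eligibility criteria adds: "The Investigator will take written informed consent from the parents of the hospitalized children".

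**Scoring of outcomes.** The allocation section promises: "The outcome assessors and data analysts will be blinded". It also separates research assistants, trained for the intervention, from assessors, trained for the baseline and endline assessments. The text after Figure 2 says that assessors contact control families, at baseline and endline only, and that the intervention team does not interact with them.

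Other places read differently. The text after Figure 1 says: "The trained and certified Research Assistants will deliver the intervention in hospital setting and then at home visits". Data collection and management, directly below the list of outcome instruments, says: "The research assistants will be trained on the use of all these tools", and adds inter-rater and intra-rater scoring exercises. Criteria for group sessions at the hospital says: "The home visits will be scheduled for the assessment of Home Environment and Parent-Child Interactions".

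**The concern.** Concealment protects the comparison only if whoever decides which families to approach, and how to seek their consent, cannot know the next assignment. Here the author of the list has that responsibility. Children likely to do well, or families likely to cooperate, could be steered towards one arm, and no later analysis can reliably detect or undo that.

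Milestone checklists, socio-emotional profiles and observed parent-child interaction all involve judgement by the rater. A rater who has delivered the sessions knows the arm and may want the programme to succeed. If such a rater scored the development outcomes, the difference between arms would mix a treatment effect with a rating effect, most plausibly in favour of the intervention. A larger sample would not remove it.

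**Working it through.** **(a) Concealment: the roles set side by side**

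| Task | Who | Where |
|---|---|---|
| Generates the sequence | Principal Investigator | Assignment of interventions |
| Identifies recruits, takes consent | Principal Investigator | Oversight and monitoring |
| Takes written consent | The Investigator | Eligibility criteria |
| Enrols and assigns | Trained assistants, with sealed envelopes | Assignment of interventions |

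An opaque envelope conceals its content from someone who has not seen the list. It therefore works for the assistants and not for the investigator. Nothing in the article keeps the list from the investigator once it is made. The documents give no figure from which a resulting bias could be computed, and none is offered.

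**(b) Blinding: two sets of statements**

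- Separate roles: the allocation section (distinct assessors, blinded) and the text after Figure 2 (assessors contact controls).
- Overlapping roles: Data collection and management (research assistants trained on all tools, with rater-agreement exercises), read with the text after Figure 1 (research assistants deliver the therapy, including at home) and with the group-sessions section (home visits used for the home-environment and interaction assessments).

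Training in rater agreement is normally meant for people who will rate, so the second set conflicts with the first.

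**Size, if deliverers did score**

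The plan's own figure first: n = 2 × (1.96 + 0.84)² × 1.69² / 0.5² = 2 × 7.84 × 2.8561 / 0.25 = 179.1, hence 180 per arm. The article shows 179.37 because it rounds 1.69² to 2.86. The stated 180 is reproduced.

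Inputs:
- Two-sided 5% level, critical value 1.96 (Sample size section).
- 162 analysed per arm = 180 × 0.9, using the 10% dropout named in that section.
- No true effect, and a rating shift b of 0.1 to 0.2 SD in favour of the intervention. The shift is an assumption; the article gives no such figure.

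With n per arm and a standardised shift b, the test statistic has mean b × √(n/2). For n = 162, √81 = 9.

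False-positive rate = P(Z > 1.96 − 9b) + P(Z < −1.96 − 9b).

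- b = 0.1: P(Z > 1.06) + P(Z < −2.86) = 0.1446 + 0.0021 = 14.7%.
- b = 0.2: P(Z > 0.16) + P(Z < −3.76) = 0.4364 + 0.0001 = 43.7%.

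With all 180 per arm, √90 = 9.487, and the rates are 15.8% and 47.5%.

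For scale, the effect used in the formula is 0.5/1.69 = 0.296 SD, so the shift is 34% to 68% of it. The same section also calls the expected difference 0.5 SD; against that, the shift is 20% to 40%.

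**The case against.** **On concealment.** Assistants enrol and assign, and the envelopes are of an accepted kind. The oversight sentence is a general statement of responsibility, and Eligibility criteria says only that the Investigator takes consent. It would therefore be too strong to say that concealment is wholly defeated. The overlap still stands: the steps open to selection, identifying families and obtaining consent, are assigned to the person who made the list.

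**On blinding.** A reader might infer that therapists score their own families' development at one year. The documents do not say so. The allocation section and the text after Figure 2 name separate assessors, the sentence in the data collection section concerns training, and the one-year assessment is described without naming who does it. The sentence on home visits does not name the rater either. Neither the home-environment nor the interaction instrument is named in the Outcomes section, although parent-child interaction appears in the second primary objective. What stands is a contradiction about who uses the outcome tools.

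**On reach.** A reader might also extend the bias to every primary outcome. The second one, parental knowledge and skills, is planned for assessment in the parents of the 180 intervention children only. No between-arm comparison of it is described, so the rating-shift calculation does not apply there.

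**On the remedy.** Trial status gives recruitment from January 2023 and expected completion on 30 May 2024, and this protocol version is dated 04/10/2024. A new sequence may no longer be possible. The group-sessions section also describes randomisation before written consent, and Eligibility criteria draws controls from another ward in periods without intervention. Either could reveal the arm at consent whoever makes the list. Both need separate attention.

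**Conclusion.** The concealment part holds on the text: one person makes the sequence and is responsible for identifying recruits and taking consent, and envelopes do not hide the list from that person. This shows that selection at consent was possible, not that it happened.

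The blinding part holds as an internal contradiction. The claim of blinded assessment cannot be relied on until the passages are reconciled. The increase in the false-positive rate from 5% to about 15% to 44% for a between-arm development score rests on three conditions: research assistants do score, their ratings shift by 0.1 to 0.2 SD towards the intervention, and 162 per arm are analysed with no true effect. It says nothing about the size of any bias from the concealment gap.

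**What to change.** **Allocation.** Have existing staff with no recruitment, consent or analysis role generate the sequence and prepare the envelopes. Keep the list from the Principal Investigator and the enrolling staff until database lock. If recruitment is already complete, report who made and held the list, and do not claim full concealment.

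**Scoring.**
- In Data collection and management, change research assistants to assessors in the sentence on training in the tools.
- State that all baseline, 6-month and 12-month outcome scores, in both arms, come only from assessors who deliver no sessions.
- Reconcile the text after Figure 2, which limits assessor contact with controls to baseline and endline, with the six-month assessment in Eligibility criteria.
- Treat scores that research assistants record at home visits as process data. If outcomes have already been collected, report who scored each one and label any scored by deliverers as unblinded.

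**Cost.** Tasks move among existing staff and a few sentences change. The monthly scores recorded by research assistants are lost as outcome data.
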